## 1. Background and purpose of this study

Liver metastasis is a major limiting factor to the prognosis of colorectal cancer. Recently the progressive surgical removal of metastatic liver tumors becomes practical because of development of intraoperative ultrasound technique and improves survival rate when they are resectable.

Even in unresectable cases there are reports of efficacy of intra hepatic arterial infusion of chemotherapeutics (HAI), trans-arterial embolization (TAE) and microwave coagulation necrosis (MCN).

To contribute to better result after surgical removal of metastatic liver metastases it is inevitable to control metastasis in the residual liver and extra-hepatic metastasis especially to lungs.

We have tried to use intra- hepatic arterial infusion of 5-FU to control metastasis in the residual liver but the hepatic arterially infused 5-FU is not expected to work on extra-hepatic metastases because it is deactivated in liver. The systemic chemotherapy should be added to this situation but the application of cytotoxic chemotherapeutics in early postoperative stage is not practical at all from the point of their adverse effects.

Antineoplastons are naturally occurring peptides and amino-acid derivatives which control neoplastic growth and have been found in blood and urine under the concept of biochemical defense against cancer. They work on divert mechanism of action. Researchers reported its antagonism against chemical and viral carcinogen, competitive up take of tumor cells against l-glutamine which is nitrogen source to tumor cells which lead G1 arrest in tumor cells, induction of cell differentiation in tumor cells, deactivation of oncogenes, activation of tumor suppressor genes through the alteration in DNA methylation status. And most of all they are quite non-toxic.

Antineoplastons could be combined with other chemotherapy because of less toxicity and also restored effect of chemo-resistance in tumor cells could be expected by Antineoplastons.

Phase I toxicological clinical study conducted in Kurume University Hospital from 1988 showed only minor adverse effects such as skin rash, excess gas, rigid finger, headache, lowered cholesterol.

We experienced a case of long term survive from multiple liver metastases from colon cancer. This case motivated us to conduct this study to evaluate efficacy of Antineoplaston A10 and AS2-1 as adjuvant therapy after hepatectomy for liver metastases from colorectal cancer.

## 2. Protocol Summary

- 1) Study Design: This is randomized phase II clinical trial

- 2) Purpose: Evaluation of anti-tumor efficacy against postoperative intra and extra hepatic metastasis and toxicity of Antineoplaston A10 and AS2-1 in colorectal cancer.
- 3) Eligibility: Eligible patients had histologically confirmed metastatic colorectal adenocarcinoma to the liver. Patients were treated with R0 resection of liver metastases and/or complete ablation by radio frequency interstitial ablation therapy between April 1998 and August 2004 at Kurume University Hospital.
- 4) Treatment: In control group, patients received HAI with 5-FU at a dose of 1000 mg/m^2 for 4 hours weekly or biweekly after hepatectomy until the cumulative dose reached up to 15,000 mg.  
In Antineoplaston group, Antineoplaston A10-Injection and AS2-1 were administered from day 15 after liver surgery in addition to HAI same as in control group with a starting dose of 30 g/day of intravenous A10-Injection using a pump system to maximum dose of 100 g/day for more than 3 days. After completion of the i.v. administration of A10-Injection for a week, 10 g/day of AS2-1 was administered orally for 1 year.
- 5) Primary Study Endpoints: The efficacy and safety endpoints will be Cause-specific survival rate, Disease free survival rate, Degree of recurrence, frequency, severity of adverse events.
- 6) Total number of patients: a total of 50 patients will be enrolled with 25 patients randomized to one of two treatment groups.
- 7) Duration of Study: The study will conduct from April 1998 to December 2004 and the prognosis of patients will be followed for at least 5 years.

### 3. Purpose of the study

To test efficacy and safety of Antineoplaston A10 and AS2-1 in adjuvant use in addition to HAI (5-FU) after hepatectomy for metastatic liver cancer from colon.

### 4. Eligibility

#### 1) Inclusion Criteria

Patient who underwent curative hepatectomy or thermal ablation for liver metastases histologically confirmed as a metastasis from colon.

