**Hepatic arterial infusion of 5-FU**

5-FU is administered through a catheter instituted in hepatic artery, confirmed the position by angiogram, in early post-operative stage after hepatectomy either intermittently (1000 mg/m^2/ for 4 hours/1-2 weeks) or continuously 180 mg/day. Continuous infusion of 5-FU may interrupt one week. Administration of 5-FU ends with total dose 15 g infused.

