**Antineoplaston A10 Injection and AS2-1**

On 15th day after liver surgery Antineoplaston A10 Injection (30 g/day) starts to be infused through the catheter instituted in great vein and increase the dose up to maximum 100 g/day and keep this dose for 3 days. Then Antineoplaston AS2-1 10 g/day (at breakfast, lunch, dinner and before sleep) starts to be administered and continued for one year.

8. Randomization

Eligible patients are randomly assigned to receive systemic antineoplastons plus 5-FU HAI (AN arm) or 5-FU alone (control arm) by minimization method using number of metastases (1-3 vs >4) and presence or absence of prior extra-hepatic metastases which were removed completely at the time of surgery.

9. Drugs during the study period

No other anti-cancer drugs should be used during the study period.

No limitation of use of anti-histamine or digestive medication is applied.

10. Therapy during the study period

Chemotherapy, immunotherapy and radiotherapy are not conducted during the study period. When any of those therapies has conducted with un-avoidable reason the content of the conducted therapy, when it has conducted and details of course history should be recorded.

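### Ablation-only patients are eligible, but the stated purpose and the HAI timing refer only to hepatectomy, and the minimisation leaves procedure to chance

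*Protocol*

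**What the plan says.** **Population in the aim and purpose.** Section 1 ends with the aim of evaluating the drugs "as adjuvant therapy after hepatectomy for liver metastases from colorectal cancer". Section 3 states the purpose as testing them "in adjuvant use in addition to HAI (5-FU) after hepatectomy for metastatic liver cancer from colon". Neither mentions ablation. The purpose item in the summary, Section 2(2), is looser and speaks only of postoperative metastasis.

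**Population in the eligibility.** Section 4 admits a "Patient who underwent curative hepatectomy or thermal ablation for liver metastases histologically confirmed as a metastasis from colon". Section 2(3) says "Patients were treated with R0 resection of liver metastases and/or complete ablation by radio frequency interstitial ablation therapy", which covers resection alone, ablation alone, or both.

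**Treatment timing.** HAI is given to both arms. Section 2(4) schedules it "for 4 hours weekly or biweekly after hepatectomy until the cumulative dose reached up to 15,000 mg", and Section 7 places it "in early post-operative stage after hepatectomy either intermittently" or continuously. The antineoplaston start is counted from a different event: both sections set it on day 15 after liver surgery, without saying whether ablation counts as liver surgery.

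**Allocation.** Section 8 assigns patients "by minimization method using number of metastases (1-3 vs >4") and on the presence or absence of completely removed extra-hepatic metastases. Procedure is not a factor.

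**The concern.** There are two linked problems.

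The first is one of definition. The purpose names patients after hepatectomy, while the eligibility names a wider group. A reader of the result could not tell from the protocol which population the conclusion is meant for. An ablation-only patient also has no hepatectomy from which to count the HAI schedule.

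The second is one of precision. Section 14 compares cause-specific survival and time to intra-hepatic and extra-hepatic recurrence. Time to intra-hepatic recurrence in particular may plausibly depend on how the liver lesions were cleared. With 50 patients and no balancing on procedure, the arms can differ noticeably in their share of ablated patients. If procedure is prognostic, that difference moves the contrast between arms without any drug effect.

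**Working it through.** **Step 1: the passages side by side**

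| Place in the protocol | Population or anchor |
|---|---|
| Section 1, aim | after hepatectomy |
| Section 3, purpose | after hepatectomy |
| Section 2(2), summary purpose | postoperative, procedure not named |
| Section 2(3), summary eligibility | resection, ablation, or both |
| Section 4, inclusion | hepatectomy or thermal ablation |
| Sections 2(4) and 7, HAI | after hepatectomy |
| Sections 2(4) and 7, antineoplastons | day 15 after liver surgery |
| Section 8, minimisation | number of metastases; removed extra-hepatic disease |

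The two eligibility statements agree that ablation alone qualifies. The aim, the purpose and the HAI timing were not aligned with them.

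**Step 2: the plan's own figure**

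Section 17 gives 25 patients per group for significance at 5-year survival. It states no significance level, sidedness, power, control rate or effect, so the figure cannot be reproduced. For scale only: with an assumed control survival of 20–50%, two-sided 5% and 80% power, 25 per arm corresponds to a difference of about 36–39 points without continuity correction.

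**Step 3: chance imbalance in procedure**

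Inputs: 50 patients, 25 per arm (Sections 2(6) and 17). The number K of ablated patients is not given, so 5 to 25 (10–50%) is assumed. Procedure is taken as unrelated to the two existing minimisation factors. The number x of ablated patients in one arm is then hypergeometric, and the difference in share between arms is |2x − K| / 25. A difference of at least 20 points means at least 5 patients.

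Standard deviation of the difference in share = (2/25) × √[25 × (K/50) × (1 − K/50) × 25/49].

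| K (assumed) | Share | SD of difference | Smallest count that qualifies | P(difference ≥ 20 points) |
|---|---|---|---|---|
| 5 | 10% | 8.6 points | 5 | 0.050 |
| 10 | 20% | 11.4 points | 6 | 0.074 |
| 15 | 30% | 13.1 points | 5 | 0.217 |
| 20 | 40% | 14.0 points | 6 | 0.148 |
| 25 | 50% | 14.3 points | 5 | 0.258 |

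Hand check for K = 5: all five must fall in one arm, so P = 2 × C(25,5)/C(50,5) = 2 × 53,130/2,118,760 = 0.050.

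The probabilities do not rise smoothly because of parity. With an even K the count difference is even, so at least 5 becomes at least 6 (24 points).

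**Step 4: effect on the survival contrast**

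Shift = difference in share × prognostic gap. The gap is assumed to be 10–30 points in 5-year survival.

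- Imbalance of 5 patients: 0.20 × 0.10 to 0.20 × 0.30 = 2 to 6 points.
- Imbalance of 8 patients (probability at most about 4%): 0.32 × 0.10 to 0.32 × 0.30 = 3.2 to 9.6 points.

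**Step 5: comparison with sampling error**

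Assume 5-year survival of 30–50% in both arms and no earlier censoring. The standard error of the difference is √[2p(1 − p)/25]: √(0.42/25) = 0.130 at 30% and √(0.50/25) = 0.141 at 50%, or about 13–14 points. A 6-point shift is under half of that.

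**The case against.** Admitting ablation is plainly deliberate, since both eligibility statements do so. The summary purpose is not limited to hepatectomy, and liver surgery is a broader term than hepatectomy. On this view only loose wording remains. Leaving one more covariate to chance is not an error, because randomisation balances it in expectation and number of metastases may balance it in part. Any adjustment in the analysis can be left to a statistical analysis plan that is not shown. The size of the problem rests on two assumed inputs.

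Most of this stands, and it limits the point. In particular, three stronger readings are tempting but not supported:

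- *That the background marks ablated patients as a worse-prognosis group.* Section 1 lists microwave coagulation among options for unresectable disease, but HAI is on the same list ("Even in unresectable cases there are reports of efficacy of intra hepatic arterial infusion of chemotherapeutics (HAI") and every trial patient receives HAI. Eligible ablation is by radiofrequency and must be complete. The protocol never compares outcomes after resection and ablation.
- *That the comparison is biased.* Any imbalance arises by chance and has no expected direction.
- *That the trial cannot inform on hepatectomy patients.* They are enrolled and randomised, and contribute to an average effect over the mixed population.

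The objection does not dispose of the inconsistency itself. An analysis plan could adjust for procedure, but it could not change the stated purpose, the event from which treatment is counted, or the allocation rule. The absence of an analysis stratum is not itself part of this point.

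**Conclusion.** The inconsistency is in the text and needs no assumption: ablation-only patients are eligible, while the aim, the purpose and the HAI timing refer to hepatectomy alone. The omission of procedure from the minimisation is a missed cheap improvement, not a flaw that invalidates the comparison.

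Under the assumptions stated in the working, a 20-point imbalance has a 5–26% chance and would shift the contrast by about 2–6 points. That is modest beside both the standard error and the large difference that 25 per arm could detect. The shift would be smaller if procedure is related to number of metastases and so already partly balanced, or if the prognostic gap is small. The point merits correction chiefly because the population to which the conclusion applies should be stated once and consistently.

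**What to change.** 1. In Section 8, add a third two-level minimisation factor: hepatectomy only versus any thermal ablation. Procedure is known before randomisation because eligibility requires it to have been done, and this split gives patients who had both a defined level.
2. Account for the same factor in the Section 14 comparison.
3. Make Sections 1 and 3 and the inclusion criterion in Section 4 name the same population. If ablation is intended, as both eligibility statements suggest, the purpose should say so.
4. Reconcile the HAI passages (Sections 2(4) and 7), counted from hepatectomy, and the antineoplaston passages, counted from liver surgery, with the eligibility of ablation-only patients. Which timing applies is for the investigators; none is proposed here.

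Cost: one more factor in the existing minimisation and some wording edits, with no added patients, visits or tests. The downside is slightly looser balance on the two existing factors.

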#### 2) Exclusion Criteria

- a) Patient who received other anti-tumor medication, differentiation inducer, radiotherapy at least in the recent 4 weeks.
- b) Patient in severe major organ dysfunction.
- c) Patient whose age over 75 years-old.
- d) Patient whose ECOG physical status over 3.
- e) Patient who do not tolerate HAI of 5-FU.
- f) Patient who has extra-hepatic lesion or other type of cancer.
- g) Patient who is pregnant or possibly pregnant.
- h) Patient whose WBC less than  $3,000/\text{mm}^3$
- i) Patient whose neutrophile less than  $1,500/\text{mm}^3$
- j) Patient whose platelet less than  $75,000/\text{mm}^3$
- k) Patient whose GOT,GPT over 100 IU
- l) Patient whose total bilirubin over 2.0 mg/dl
- m) Patient whose creatinine over 1.5 mg/dl
- n) Patient whom attendant investigator judges not appropriate to undergo this trial.

## 5. Informed Consent

It is the responsibility of the investigator to provide oral and written information about this study and obtain to obtain a signed informed consent from each patient participating with free will in this study prior to enrollment.

In case of the patient who is unable to understand what this study about, informed consent should be obtain from a person representing patient benefit legally. In case of the patient whose age is under 20 years informed consent should be obtained from the patient and legal representative.

The following issues should be fully explained before getting informed consent.

- 1) The purpose and method of this study.
- 2) Expected efficacy and toxicity.
- 3) Other therapeutic modalities could be applied to the disease.
- 4) Patient do not get disadvantage when he(she) do not anticipate to this study.
- 5) Patient can decline participating to this study treatment anytime after he or she sign the informed consent.
- 6) Patient should not claim compensation for any result from this study.
- 7) Necessary consideration for protecting patient's human right.

Informed consent should be in document, clearly noted that signed by the patient him (her) self or legal representative and the name of attendant investigator

physician and the date of informed consent obtained.

6. Investigational Drugs

Antineoplaston A10 Injection

(4:phenylacetylglutamine+1:phenylacetylisoglutamine) (300mg/ml)

Antineoplaston AS2-1

(1:phenylacetylglutamine+4:phenylacetic acid) (500mg/capsule)

Provided by Burzynski Research Institute, INC.

7. Administration

**Hepatic arterial infusion of 5-FU**

5-FU is administered through a catheter instituted in hepatic artery, confirmed the position by angiogram, in early post-operative stage after hepatectomy either intermittently (1000 mg/m^2/ for 4 hours/1-2 weeks) or continuously 180 mg/day. Continuous infusion of 5-FU may interrupt one week. Administration of 5-FU ends with total dose 15 g infused.

**Antineoplaston A10 Injection and AS2-1**

On 15th day after liver surgery Antineoplaston A10 Injection (30 g/day) starts to be infused through the catheter instituted in great vein and increase the dose up to maximum 100 g/day and keep this dose for 3 days. Then Antineoplaston AS2-1 10 g/day (at breakfast, lunch, dinner and before sleep) starts to be administered and continued for one year.

8. Randomization

Eligible patients are randomly assigned to receive systemic antineoplastons plus 5-FU HAI (AN arm) or 5-FU alone (control arm) by minimization method using number of metastases (1-3 vs >4) and presence or absence of prior extra-hepatic metastases which were removed completely at the time of surgery.

9. Drugs during the study period

No other anti-cancer drugs should be used during the study period.

No limitation of use of anti-histamine or digestive medication is applied.

10. Therapy during the study period

Chemotherapy, immunotherapy and radiotherapy are not conducted during the study period. When any of those therapies has conducted with un-avoidable reason the content of the conducted therapy, when it has conducted and details of course history should be recorded.

#### 11. Observation and time schedule for tests

##### 1) Patient information before the study treatment

Name of patient (initial), gender, age (date of birth), in-patient or out-patient

Clinical diagnosis, histological diagnosis, clinical stage, physical status, disease history before treatment, past history of disease and allergy

##### 2) Previous treatment to the present disease

##### 3) Time schedule of observation and tests

|                | control | 1month | 2month | 3month | 6month | 9month | 12 month | Every 3 month |
|----------------|---------|--------|--------|--------|--------|--------|----------|---------------|
| AS2-1          |         | →      | →      | →      | →      | →      | →        | →             |
| Symptoms       | ○       | ○      | ○      | ○      | ○      | ○      | ○        | ○             |
| Recurrence(CT) | ○       | ○      | ○      | ○      | ○      | ○      | ○        | ○             |
| Clinical tests | ○       | ○      | ○      | ○      | ○      | ○      | ○        | ○             |
| Tumor marker   | ○       | ○      |        | ○      | ○      | ○      | ○        | ○             |
| Frozen Serum   | ○       |        |        |        |        |        |          |               |
| E.C.G.         | ○       |        |        |        |        |        | ○        |               |

##### 4) Subjective and objective symptoms

Subjective and objective symptoms related to treatment are graded according to the Common Terminology Criteria for Adverse Events (CTCAE version 2 provided by Japanese Society of Cancer Therapy ) for toxicity and adverse

events reporting.

Any abnormal symptom should be graded in relation of treatment into 4 categories: 1. obviously related 2, probably related. 3. possibly related 4. Not related

5) Search for recurrence and metastasis

Ultrasound sonography, CT to search recurrence and metastasis, should be conducted at least once every 3 months in post-operative 2 years and thereafter at least once every 6 months up to 5 years.

The location, number, size and extent of recurrence and metastasis should be examined and recorded.

6) Clinical tests and physical examination

The following clinical tests and physical examination are carried out pretreatment, one month after treatment and thereafter every 3 months. Any abnormal finding of these tests and examination found after treatment should be graded to 4 categories: 1. obviously related 2, probably related. 3. possibly related 4. Not related

- a) Physical examination: blood pressure, heart rate, Performance Status
- b) Hematology: WBC count, fraction of WBC, RBC count, Hb, Ht, Platelet count
- c) Serological tests: GOT, GPT, ALP, LDH,  $\gamma$ GTP, ChE, Total bilirubin, direct bilirubin, total protein, albumin, total cholesterol  
BUN, creatinine, uric acid, Na, K, Cl, Ca, P, blood glucose amylases, ICG, HPT, PT
- d) Urological tests: protein, glucose, urobilinogen
- e) Electrocardiogram

7) Tumor marker

CEA should be measured prior to treatment, one month after treatment and thereafter once every 3 months.

8) Preserve frozen serum

The patient's serum is preserved frozen for measurement of newly developed tumor marker or additional tests necessary in future.

9) Adverse events

Adverse events other than subjective and objective symptoms happening during the study period should be graded in severity according to CTCAE version 2 and recorded with date, time of event and treatment and response.

10) Diary

Patient is requested to record any abnormal symptom, frequency of symptom, duration of symptom he (she) feels in diary.

12. Withdrawal criteria

The study should interrupt in cases with following reasons

- 1) Progressive deterioration of symptom from disease
- 2) Deterioration of general condition from complication
- 3) Appearance of unexpected event
- 4) Unable to administer testing drugs due to adverse effects
- 5) Patient or family want to withdraw from the study
- 6) Unable to follow patient
- 7) When attendant investigator judge not to continue the study

In the interrupted cases, clinical observation, physical examination and clinical tests should continue as scheduled to evaluate the efficacy and toxicity of testing drugs.

In the interrupted cases who have not visited hospital, an effort should be paid to follow up the patients to clarify the prognosis and the reason why not visiting hospital.

13. Registered patients in the study are categorized into appropriate, inappropriate, perfectly treated, imperfectly treated and appropriate perfectly treated by the standard of Japanese Cancer Patient Follow up Committee in Japanese Society of Cancer Therapy.

14. Evaluation of efficacy

Efficacy of the testing drug should be evaluated by comparing cause specific survival, time to intra-hepatic recurrence, degree of extension of recurrence and time to extra-hepatic recurrence between Antineoplatstons treated group and control group.

15. Serious adverse effects during the study should be reported immediately to the

safety committee and treated properly. The safety committee of this study consists of principal investigator and study investigators. The safety committee should be open to patient's contact 24 hours a day.

16. Follow up

Treatment of patient disease after the study completed will be depending on attendant physician's decision, the prognosis of patient will be followed up to 5 years after study treatment.

17. Sample size

Statistical consideration for obtaining significance at 5 years survival needs 25 patients in each group making total 50 patients.

18. Time to start the study

The study starts from April, 1998 for 10 years.

19. End of the study

The study will ends enrollment as soon as 50 patients finish the study treatment.

20. Recording

- 1) Recording should be written in black
- 2) Correction of description must be done by X mark or two lines with signature who made correction. The date and reason for correction must be noted if the correction is major and serious.

21. Management of testing drugs

Testing drugs are managed by a study investigator who takes care of drug management.

22. Organization of conducting this study

Lower Gastrointestinal Group in Department of Surgery, Kurume University, School of Medicine

Antineoplaston Study Group in Kurume University, School of Medicine

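### Symptoms receive a severity grade only if related to treatment, while all other adverse events are graded whatever their cause, so the symptom part of the severity endpoint rests on a causality call

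*Protocol*

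**What the plan says.** The Protocol Summary (section 2, item 5) includes "frequency, severity of adverse events" among the primary endpoints. Section 11 sets out how the data for that endpoint are collected.

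- **Item 4, symptoms, severity:** "Subjective and objective symptoms related to treatment are graded according to the Common Terminology Criteria for Adverse Events".
- **Item 4, symptoms, causality:** "Any abnormal symptom should be graded in relation of treatment into 4 categories". The last of the four categories is *not related*.
- **Item 6, tests and examinations:** "Any abnormal finding of these tests and examination found after treatment should be graded to 4 categories". This is again a causality scale; the item names no severity grade.
- **Item 9, everything else:** "Adverse events other than subjective and objective symptoms happening during the study period should be graded in severity according to CTCAE version 2". No condition on cause is attached.
- **Item 10, diary:** the patient notes abnormal symptoms with their frequency and duration. Severity is not asked for.

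Section 8 compares antineoplastons plus hepatic arterial infusion (HAI) of 5-FU with HAI alone. No placebo or blinding is described. The protocol does not say who makes the causality call or which treatment it refers to.

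**The concern.** Two rules for one endpoint leave a hole. A non-symptom event is graded for severity whatever its cause. A symptom is graded only after it has been attributed to treatment. Whether a severe headache appears in the severity table then depends on a judgement about its cause.

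That judgement can go either way. An assessor who knows that a patient is on an investigational drug may attribute background symptoms to it more readily, which makes the antineoplaston (AN) arm look worse. An assessor who shares the Background's view that the drugs have little toxicity may call the same symptoms unrelated, which removes them from the table and makes that arm look better. Section 15 offers no independent check, because the safety committee consists of the principal investigator and the study investigators.

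The loss is permanent. A grade that was not recorded at the time cannot be restored by any later analysis.

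**Working it through.** **1. Which events get a severity grade.** Items 4 and 9 of section 11, read as written:

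| Event | Causality category | Severity grade |
|---|---|---|
| Symptom, judged related in some degree | yes (item 4) | yes (item 4) |
| Symptom, judged not related | yes (item 4) | **none**: item 4 covers related symptoms and item 9 excludes symptoms |
| Other adverse event, any cause | not required by item 9 | yes (item 9) |

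The second row is the gap. The diary does not fill it, since it holds no severity.

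**2. How much of the expected toxicity is symptomatic.** The Background names five adverse effects from the earlier phase I study. Rash, gas, finger stiffness and headache are symptoms or signs; reduced cholesterol is a laboratory finding. So 4 of 5 fall mainly under item 4.

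**3. What the filter does to the comparison.** Suppose both arms have the same symptoms with the same severity, and let q be the share judged related. The ratio of graded symptoms, AN to control, is then q(AN) / q(control), where the true ratio is 1. The protocol fixes neither share, so the ratio can lie on either side of 1.

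**4. Length of trial treatment.** HAI ends at a total of 15,000 mg in both arms (sections 2 and 7). Body surface area is not given; 1.4–2.0 m² is assumed.

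*Intermittent:* number of infusions n = 15,000 / (1000 × area), rounded up; weeks from first to last = (n − 1) × interval.

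| Area (m²) | 15,000 / (1000 × area) | n | Weekly | Every 2 weeks |
|---|---|---|---|---|
| 1.4 | 10.7 | 11 | 10 weeks | 20 weeks |
| 1.6 | 9.4 | 10 | 9 weeks | 18 weeks |
| 1.8 | 8.3 | 9 | 8 weeks | 16 weeks |
| 2.0 | 7.5 | 8 | 7 weeks | 14 weeks |

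*Continuous (section 7):* 15,000 / 180 = 83.3 days = 11.9 weeks. If the permitted one-week interruption is read as every second week off, this becomes 2 × 11.9 − 1 = 22.8 weeks.

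The control range is thus 7 to 22.8 weeks, or 7 × 7 / 30.44 = 1.6 months to 22.8 × 7 / 30.44 = 5.2 months. The AN arm has at least 52 weeks of AS2-1. The ratio of treatment lengths runs from 52 / 22.8 = 2.3 to 52 / 7 = 7.4.

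This is a ratio of exposure times. It is not an estimate of bias. It would carry over to graded symptoms only if relatedness followed on-treatment status exactly, and the protocol does not say that it does.

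**The case against.** **Only part of the endpoint is affected.** Item 9 grades all non-symptom events regardless of cause. This stands: the defect is confined to the severity of symptoms judged not related.

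**Frequency is intact.** Item 4 classifies every abnormal symptom, the diary records frequency and duration, and the observation schedule in section 11 is the same for both arms. This also stands. An unrelated symptom is still recorded; it lacks only a grade.

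**The restriction may be loose English.** Item 9 treats symptoms as already dealt with, which suggests that the authors thought item 4 graded them all. That is possible, but the sentence right after the restriction says that any abnormal symptom is to be classified for causality, so the authors had the wider wording at hand. Even on the mild reading the text needs correcting, because staff will follow it as written.

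**A reader might infer a several-fold artificial difference in graded symptoms from the unequal treatment lengths.** The documents do not support this. They set no on-treatment window for attribution and do not stop symptom observation when HAI ends. Longer exposure is also inherent in an add-on regimen and is not created by item 4.

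**A reader might also state as fact that the assessor knows the arm.** The protocol does not say who judges causality. With no placebo, and with a central venous infusion and a year of capsules in one arm only, it is a strong inference but no more than that.

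**How to compare events between arms can be left to the SAP.** This is fair for the analysis. It does not apply to the grading rule, which decides what data exist to be analysed.

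**Conclusion.** The point holds in a limited form. Items 4 and 9 of section 11 set different severity rules, and a symptom classified as not related receives no severity grade under either. The effect is confined to the symptom component of a listed primary safety endpoint, but that component covers most of the toxicity that the protocol itself names (4 of 5 effects).

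The direction of any bias is open and its size unknown, because the protocol gives no basis for the share of symptoms judged related in each arm. The unequal treatment lengths (about one year against roughly 2 to 5 months, at the assumed body surface area) could widen an imbalance but do not quantify it. The conclusion rests on the literal wording of item 4, and the risk of bias on the inference that causality is judged with the arm known. It should be corrected: the loss cannot be made good at analysis and the remedy is small.

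**What to change.** Reword section 11, item 4 to match item 9: *All subjective and objective symptoms are graded for severity by CTCAE irrespective of relation to treatment; relation is recorded separately.* Compare all-cause graded events between the arms, with treatment-related events as a secondary comparison; this second step can sit in the SAP.

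The cost is one extra grade per symptom. Every abnormal symptom is already recorded and classified for causality, so no new visit or test is needed and no clinical management changes. If grading has already been done under the present wording, report by arm how many symptoms were classified as not related and left ungraded, so that a reader can see how much the severity table omits.
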